### Methods in analysis to handle protocol non-adherence and any statistical methods to handle missing data {20c}

Patients who discontinue the clinical trial participation prematurely after randomization will not be replaced, whereas patients who drop out before randomization will be replaced. For the analysis of outcomes with missing data, the missingness generating mechanism will be evaluated and multiple imputation techniques will be applied.

### Plans to give access to the full protocol, participant-level data, and statistical code {31c}

The full protocol is summarized here and will be published together with the final publication; participant-level dataset and statistical code are available upon reasonable request.

### Composition of the data monitoring committee, its role, and reporting structure {21a}

*Data and Safety Monitoring Board (DSMB) members*: [name] (chair), [name], [name].

*Monitoring institution*: Clinical Trials Center – Monitoring, Universitätsspital Zürich, [name].

The DSMB will review the results of the safety assessment conducted after the completion of the 12-month follow-up of multiples of 150 patients. The DSMB can recommend continuation or termination of the study based on the evaluation of the results. An internal Clinical Events Committee made up of two clinicians will categorize the components of the primary outcome. An external Clinical Events Committee was deemed not necessary given the “hard” nature of the primary outcome, a composite of endovascular or surgical target lesion re-vascularization for critical limb ischemia and unplanned major amputation of the target limb. The Clinical Events Committee will meet regularly to review and adjudicate all clinical events. The investigator’s site will collaborate with the Clinical Trials Center (CTC) of the University Hospital Zurich ([name]) to ensure regular monitoring. According to the CTC’s Monitoring SOP, the extent and nature of monitoring activities based on the objective and design of the study are defined in a separate study-specific monitoring plan.

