### Outcomes {12}

#### Primary outcome

The primary efficacy outcome is a composite of two major adverse limb events (MALE), assessed within 1 year of randomization: an unplanned major amputation of the target limb and an endovascular or surgical target lesion re-vascularization for critical limb ischemia.

An unplanned major amputation is defined as any amputation above the ankle on the target limb, which was not planned or not expectable at the time of screening or randomization. Patients with scheduled amputation undergoing re-vascularization to improve wound healing are referred to as planned amputation and will not count for the primary outcome. Critical limb ischemia is primarily defined according to a Fontaine stage (stages III and IV).

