## Assignment of interventions: blinding

### Who will be blinded {17a}

The trial is conducted as an open-label study.

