### Confidentiality {27}

Direct access to online source documents will be permitted for purposes of monitoring, audits, and inspections. The investigator-sponsor, all investigators, the members of the clinical event committee, the study coordinator, and the bio-statistician will have access to the investigation plan and data sets during and after the study. The bio-statistician will have access to the statistical code.

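### What counts as a primary event depends on clinical judgement, yet the protocol states no masking for the two internal adjudicators and gives them the data sets during the trial

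*Protocol article*

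**What the plan says.** **The outcome.** Under Primary outcome, a major amputation of the target limb counts only if it was one "which was not planned or not expectable at the time of screening or randomization". Patients already scheduled for amputation, who are re-vascularized to help the wound heal, "are referred to as planned amputation and will not count for the primary outcome". A target lesion re-vascularization counts only if done for critical limb ischemia, and "Critical limb ischemia is primarily defined according to a Fontaine stage (stages III and IV"). Under Secondary outcomes, the same procedure at Fontaine I–II is a secondary outcome only.

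**Who decides.** Section {21a} states: "An internal Clinical Events Committee made up of two clinicians will categorize the components of the primary outcome". It adds: "An external Clinical Events Committee was deemed not necessary given the" hard nature of the outcome. It also states: "The Clinical Events Committee will meet regularly to review and adjudicate all clinical events".

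**Masking and access.** The whole answer to Who will be blinded {17a} is: "The trial is conducted as an open-label study". Confidentiality {27} grants access to the sponsor-investigator and to every investigator, and its list then goes on: "the members of the clinical event committee, the study coordinator, and the bio-statistician will have access to the investigation plan and data sets during". The same access continues once the trial has ended.

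**By-arm results.** Statistical methods {20a}, Interim analyses {21b} and the interim scenario table provide for an unblinded comparison of MALE by arm at interim only if the pooled event rate exceeds 10%.

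**The concern.** The case for doing without an external committee rests on the outcome being hard, and sections {18a} and {18b} call the risk of reporting bias minimal partly for that reason. The procedures are hard facts; the qualifiers are not. A re-intervention at the border of Fontaine II and III is a primary event on one side of the line and not on the other. Background {6a} describes critical limb ischemia as resting pain and tissue damage, so part of that line is a reported symptom. The word *expectable* leaves room for a view formed after the event, and the article names no pre-randomization record that would settle it.

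If the people who apply these qualifiers know the arm, events can move in or out of the primary outcome differently by arm. Even loss that is equal in both arms shrinks an absolute risk difference, and with a fixed 5-point margin that favours non-inferiority. The Background itself faults earlier trials for surrogate and rather subjective outcomes that are hard to adjudicate objectively in an open-label setting.

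The data-access sentence also conflicts in spirit with the interim plan. Conditional unblinding of MALE by arm means little if investigators and adjudicators can already open the data sets.

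**Working it through.** **Inputs from Sample size {14}:** 10% MALE in both arms, margin 5 percentage points (absolute), one-sided alpha 2.5%, power 80%, 566 per arm, 5% drop-out, 1200 randomized. **Assumed:** the share of events classed out of the primary outcome, for which the documents give no figure.

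**Step 1: the plan's own figure.** n per arm = (1.960 + 0.842)² × (0.10×0.90 + 0.10×0.90) / 0.05² = 7.849 × 0.18 / 0.0025 = 565.1, so 566 per arm and 1132 in total, as stated. 1132 / 0.95 = 1192, in line with the 1200 planned. The sample size is not in dispute.

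**Step 2: chance of declaring non-inferiority.** P = Φ[(0.05 − (pₑ − p_c)) / SE − 1.960], with SE = √{[p_c(1 − p_c) + pₑ(1 − pₑ)] / 566}, where pₑ and p_c are the rates as classified. Check: pₑ = p_c = 0.10 gives SE 0.01783 and P = 80.1%, the planned power.

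**Step 3: sirolimus truly worse by the whole margin (15% vs 10%; about 85 sirolimus-arm events).** P is now the false non-inferiority rate.

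| Share classed out | pₑ | p_c | SE | P |
|---|---|---|---|---|
| none | 0.1500 | 0.100 | 0.01960 | 2.5% |
| 5%, sirolimus arm only (about 4 events) | 0.1425 | 0.100 | 0.01936 | 5.8% |
| 10%, sirolimus arm only (about 8) | 0.1350 | 0.100 | 0.01911 | 12.0% |
| 20%, sirolimus arm only (17) | 0.1200 | 0.100 | 0.01859 | 36.5% |
| 10%, both arms | 0.1350 | 0.090 | 0.01874 | 4.5% |
| 20%, both arms | 0.1200 | 0.080 | 0.01779 | 8.1% |

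For the 10% one-arm row: (0.05 − 0.035) / 0.01911 − 1.960 = −1.175, and Φ(−1.175) = 12.0%.

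**Step 4: the superiority test on MALE.** With equal true rates of 10%, classing out 5%, 10% or 20% of sirolimus-arm events only gives a false superiority rate of 4.7%, 8.3% or 21.7% instead of 2.5%.

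**Step 5: the opposite direction.** Bias can also run against the device. With equal true rates of 10%, over-counting sirolimus-arm events by 5% or 10% (pₑ = 0.105 or 0.110) lowers power from 80.1% to 70.4% or 59.3%.

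**Step 6: the access provisions side by side.** Section {27} opens the data sets to all investigators and to the committee during the study, without excluding allocation. Sections {20a} and {21b} make the by-arm MALE comparison conditional on a pooled rate above 10%. Read literally, the first allows at any time what the second allows only under a condition.

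**The case against.** Three stronger readings are tempting, and the documents do not support them.

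*That adjudicators are known to see the allocation.* No sentence says so. Open-label describes the trial, and the data-access sentence does not mention allocation. The article condenses a fuller protocol, and a committee charter could provide masking. The conditional unblinding of MALE shows that some shielding of arm-level results is intended. What stands is that the access sentence, followed as written, allows classification with knowledge of the arm.

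*That the outcome is simply subjective.* Tissue damage is visible, a scheduled amputation can be checked in records, and the amputation judgement is anchored to screening or randomization. The Background's criticism was aimed at surrogate outcomes, which these are not. Judgement enters mainly at the Fontaine II/III border and through *expectable*, and the share of events falling there is unknown.

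*That the false non-inferiority rate is 12% to 36%.* Those figures assume loss in one arm only, at shares the documents do not support. Equal loss in both arms gives 4.5% to 8.1%.

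There are also safeguards. The committee already adjudicates all clinical events, and the primary endpoint is source data for monitoring. Re-vascularizations for critical and non-critical ischemia are reported separately, so a shift across the Fontaine line by arm could show. The first superiority test uses any target lesion re-vascularization and so does not depend on stage. These help detect a problem, but they do not protect the primary non-inferiority comparison. The first superiority test also keeps the *unplanned* qualifier.

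Finally, masked adjudication cannot remove bias in the open-label decision to re-intervene or in the stage the treating physician records. That is right, and it limits what the fix can achieve.

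**Conclusion.** The concern holds in a limited form. The qualifiers that decide whether an event counts need judgement, two internal clinicians apply them in an open-label trial, and no masking of them is stated. The data-access sentence allows them and all investigators to see the data sets during the study, which does not sit with the conditional unblinding at interim.

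The possible effect is material but not established. Reclassifying about 8 of some 85 sirolimus-arm events would raise false non-inferiority from 2.5% to 12.0%; about 4 events would raise it to 5.8%. Equal loss of 10% or 20% in both arms gives 4.5% or 8.1%. All of this rests on assumed shares, on true rates at the margin and on the normal approximation. No error in the sample size or the primary analysis follows. This is a cheap improvement that should be made, not a flaw that by itself invalidates the design.

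**What to change.** 1. In {21a}, state that the same two clinicians adjudicate from dossiers with allocation and device details redacted, and that this covers every target lesion re-vascularization and every target-limb amputation, not only those reported as primary events.
2. In {27}, restrict allocation-linked outcome data during the trial to the DSMB and its reporting statistician, so that access agrees with {20a} and {21b}.
3. For patients still to be randomized, record planned amputation (yes/no, level) in the eCRF before randomization. Trial status reports 396 patients enrolled by 22 December 2021, so the field cannot cover everyone. For those already enrolled, decide planned status by masked review of records dated before randomization.
4. Add a sensitivity analysis that does not use the qualifiers: any target lesion re-vascularization or any major amputation of the target limb, reported as a risk difference with the same confidence interval.

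**Cost.** Redaction work, a data-access setting, one eCRF field, a record review for enrolled patients and one extra analysis. No new committee and no change to sample size or treatment. Some dossiers will be imperfectly masked. Bias in the decision to re-intervene and in the recorded stage remains. Item 4 removes the dependence on recorded stage, but not on the decision to re-intervene, which should be acknowledged as a limitation.

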### Adverse event reporting and harms {22}

All SAEs, device deficiencies, and health hazards that require measures are reported to the sponsor by the PI (or authorized designee) within 24 h after becoming aware of the event. Device deficiencies are assessed regarding their potential to lead to an SAE. DD are assessed regarding their potential to lead to an SAE. The other study site (Fribourg) will report on SAE via RedCAP, and the sponsor will receive automatic email notification with the possibility of logging in and access the original study documents and clinical information, as provided by the investigators.

The sponsor reports to the CEC promptly any serious adverse event which has a causal relation with the MD, comparator, or procedure/test method or where a causal relation appears to be possible (Art. 33 ClinOMD). In order to ensure prompt notification, the sponsor may initially submit an incomplete notification. If safety and health hazards that require measures must be taken immediately during the conduct of the investigation, the sponsor notifies the CEC within 2 days of these measures and the circumstances which made them necessary (Art. 34 ClinO-MD). An Annual Safety Report (ASR; Art. 35 ClinO-MD) is submitted by the sponsor to the CEC, yearly. The ASR contains a list of all SADEs and DDs and a report on their degree of seriousness, causal relationship with the MD and procedure and on subjects’ safety. Other reporting is done according to provisions of MD vigilance as per Art. 87-90 MDR (Art. 33 abs 4.b ClinO-MD) and Art. 67 MedDO.

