**Fig. 1 Fig1:**
[figure not shown]
Temporal penetration of labeled sirolimus nanoparticles

In an animal study, evaluating blood and tissue levels in rabbits after treatment with Magic Touch found that blood concentration decreased rapidly after a single 60-s deployment, while tissue concentration was still detectable after 2 weeks (Fig. 2).

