### Strategies to improve adherence to interventions {11c}

Since the treatment period immediately follows randomization and ends with the termination of the re-vascularization procedure, and the investigational product does not remain in situ, there is no need to track participant compliance. The compliance of the interventionist (investigator) to the use of the respective study devices will be monitored. The erroneous use of a drug-coated balloon catheter in a patient allocated to the uncoated group and vice versa, or the use of any drug-eluting stents will be documented as a major protocol violation.

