#### Safety outcomes

The safety outcomes include the following:
Death from all causes within 30 days, 180 days, 1 year, 2 years, and 5 yearsSerious adverse events (SAEs) during initial hospitalization, within 30–180 days, and within 365 daysSerious adverse device-related events (SADE) during initial hospitalizationA composite of all-cause death and MALE within 30 days

The occurrence of safety outcomes, including vital status of patients, will be verified at each scheduled visit or time point, including hospital discharge, interim visit (day 30–180), 1-year visit (day 365 + 30), and study termination (year 5), or if it is being reported by patients at any time during follow-up.

The primary sources for verifying the patients’ vital status will be in-person contact with the relatives and treating physicians, internal and external medical reports (including discharge letters including the vital status and causes of death), and administrative vital registration data (“Zivilstand”).

A serious adverse event (SAE) is represented by an adverse event that led to any of the following:

(a) Death

(b) Serious deterioration in the health of the subject that resulted in any of the following:

(i) Life-threatening illness or injury

(ii) Permanent impairment of a body structure or a body function

(iii) Hospitalization or prolongation of patient hospitalization

(iv) Medical or surgical intervention to prevent life-threatening illness or injury or permanent impairment

to a body structure or a body function

(v) Chronic disease

(c) Fetal distress, fetal death, or a congenital physical or mental impairment or birth defect

The definitions of SADE, adverse device effect (ADE), and unanticipated serious adverse device effect (USADE) are reported in the study protocol (Supplementary Material).

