### Sample size {14}

The sample size calculation is based on previous studies reporting MALE rates in PAD patients after re-vascularization procedures. These studies were heterogeneous in study design, patient selection, techniques (proportion of patients with endovascular approach), and findings [13–24]. Hess et al. reported a MALE incidence of 10% at 12 months among 381,415 re-vascularized patients that were included in the Premier Healthcare Database between April 2009 and September 2014 [19]. In addition, there were two larger interventional studies reporting 30-day MALE incidence after surgical or endovascular therapy of symptomatic PAD patients. Fashandi et al. reported a MALE incidence of 3.2% in patients with claudication at 1 month following therapy [21]. Mehaffey et al. reported a MALE incidence of 12.2% in patients with critical limb ischemia (CLI) [22]. The COMPASS trial estimated a MALE incidence of 2.0% among 6.341 patients with PAD at 21 months, of which 35% were asymptomatic. The MALE incidence was 3.6% among the subgroup of patients with previous re-vascularization procedures [24]. A subgroup analysis of the Fourier trial estimated a MALE incidence of 1.5% among 3.642 patients with PAD (31% asymptomatic) at 12 months [23]. In the XTOSI study, the 6-month amputation-free survival was 90% in patients receiving sirolimus-coated balloon catheters.

Based on these studies, assuming a 10% event rate (MALE) within 12 months in both the control and intervention group, and a non-inferiority margin of 5% expressed as absolute risk difference, a total of 1132 patients (566 patients per treatment group) allow to show non-inferiority of the intervention group with a power of 80% and a type I error rate of *α* = 2.5% one-sided. Assuming a drop-out rate of 5%, including randomization failures, a total of 1200 patients will be randomized in the study.

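### The device-related serious event (SADE) outcome closes at the end of the index hospital stay, so after discharge no listed outcome compares the arms on events classified as device-related

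*Protocol article*

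**What the plan says.** The Safety outcomes list (Outcomes {12}) gives each outcome its own window. All-cause death is counted at five time points from 30 days to 5 years. SAEs are counted during the index stay, at 30 to 180 days and to 365 days. A composite of death and MALE is counted at 30 days. SADEs are counted during the index stay and no later. The same section then says: "The occurrence of safety outcomes, including vital status of patients, will be verified at each scheduled visit or time point", and the time points it names run to year 5. It refers the definitions of SADE and related terms to the full protocol, but it states the SADE window itself.

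Adverse event reporting and harms {22} has all SAEs reported to the sponsor. The sponsor passes on "any serious adverse event which has a causal relation with the MD, comparator, or procedure/test method or where a causal relation appears to be possible". On the yearly safety report it says: "The ASR contains a list of all SADEs and DDs and a report on their degree of seriousness", together with their causal relationship. None of these rules states a stop at discharge. The auditing section {23} names SAE/SADE among the source data.

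On drug exposure, the section on the investigational device reports from a rabbit study that "tissue concentration was still detectable after 2 weeks". Section {11c} remarks that "the investigational product does not remain in situ, there is no need to track participant compliance". The abstract's discussion and the main Discussion both say that the trial will inform on the efficacy and safety of the sirolimus-coated balloon.

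**The concern.** SADE is the only listed safety outcome defined by relation to the device, and it has the shortest window. The coating is meant to act on the vessel wall after the balloon has been withdrawn, and the article's own animal data show drug in tissue at 2 weeks. Length of stay is not given. However, the informed consent section expects elective procedures to be the most frequent case, so many stays may be shorter than that.

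An event after discharge that is judged related to the device would be reported to the sponsor and listed in the yearly report. In the defined outcomes it would appear as one SAE among all hospitalizations and other serious events, without the device label. If SAEs of any cause are common in this population, a modest late excess of device-related events would be hard to see there. No primary conclusion is at stake. The loss is in how specifically the trial can speak on device safety after discharge.

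**Working it through.** **Step 1: compare the windows.**

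| Item | Device-related label used? | Window | Source |
|---|---|---|---|
| Death, any cause | no | 30 days to 5 years | Safety outcomes |
| SAE, any cause | no | index stay, 30–180 days, 365 days | Safety outcomes |
| Death or MALE | no | 30 days | Safety outcomes |
| MALE, amputations, re-vascularizations | no | 1 year (365 days) where a window is stated | Primary and Secondary outcomes |
| SADE | yes | index stay only | Safety outcomes |
| Sponsor report of SAEs with certain or possible causal relation | yes | none stated | Section {22} |
| Yearly list of SADEs | yes | none stated | Section {22} |

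After discharge, every row that uses the device-related label is a reporting duty and every outcome row ignores the label. That is the gap.

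**Step 2: the plan's own sample size.** The inputs are "assuming a 10% event rate (MALE) within 12 months in both the control and intervention group", "a non-inferiority margin of 5% expressed as absolute risk difference", and a calculation "with a power of 80% and a type I error rate of" 2.5% one-sided.

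n per arm = (1.96 + 0.8416)² × 2 × 0.10 × 0.90 / 0.05² = 565.1, rounded up to 566, so 1132 in total. This matches the article. With 5% drop-out, 1132/0.95 = 1192, against 1200 stated. Evaluable per arm: 1200 × 0.95 / 2 = 570, used below. The sample size is not in question.

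**Step 3: illustrative precision.** The article gives no SAE or SADE rates, so every rate here is an assumption. With n = 570 per arm:

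- SE = √[p1(1−p1)/n + p2(1−p2)/n]
- 95% half-width = 1.96 × SE
- approximate power (two-sided 5%) = Φ(difference/SE − 1.96)

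Worked example for SADE at 0.5% vs 2.5%: SE = √[(0.004975 + 0.024375)/570] = 0.00718; half-width = 1.41 points; power = Φ(0.0200/0.00718 − 1.96) = 0.80.

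| Assumed rates | Excess | Half-width (points) | Power |
|---|---|---|---|
| SADE 0.5% vs 2.5% | 2 points | 1.41 | 0.80 |
| SADE 1% vs 3% | 2 points | 1.62 | 0.68 |
| SADE 2% vs 4% | 2 points | 1.98 | 0.51 |
| SADE 3% vs 5% | 2 points | 2.27 | 0.41 |
| SADE 0.5% vs 1.5% | 1 point | 1.15 | 0.40 |
| SADE 2% vs 3% | 1 point | 1.81 | 0.19 |
| SAE 30% vs 32% | 2 points | 5.37 | 0.11 |
| SAE 50% vs 52% | 2 points | 5.80 | 0.10 |

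The direction is the same throughout: the labelled outcome is more precise because its background rate is lower. The size depends on the assumed SADE rate. The SADE rows also assume that every excess event is labelled correctly and without bias, which an open-label trial cannot guarantee.

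**The case against.** Four points can be made against the concern.

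**Late harm is already compared.** A reader might infer that device harm after discharge never enters the comparison of the arms, or is visible only in the all-cause SAE count. The article does not support either reading. A SADE is an SAE, so a late one counts to 365 days. Deaths count to 5 years, and mortality is also estimated by arm after every 150 patients with 12-month follow-up. Limb harm counts in MALE, the amputation outcomes and the re-vascularization outcomes. This point stands and limits the concern to the missing classification.

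**There is no contradiction.** Section {22} describes regulatory reporting, and a reporting duty may be wider than an outcome list. That it has no time limit is read from its silence; the article does not say so outright. This stands. Section {22} shows only that the classification should be available after discharge. Verification of safety outcomes up to year 5 sits awkwardly with a window that closes at discharge, but does not contradict it.

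**The evidence for late device effects is thin.** The rabbit data show persistence of drug, not harm. A reader might cite the two major amputations for foot sepsis within 30 days among 38 patients in the first-in-human study. The article does not attribute them to the device or say that they followed discharge, and comparable unplanned events here would enter the limb outcomes anyway. This stands. In the other direction, the remark that the product does not stay in place is given as a reason not to track compliance, not as a reason for the SADE window.

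**Causality labels may be biased.** Treatment is known and only one arm carries a drug, so late events could be attributed to the device differently by arm. All-cause SAEs and deaths avoid this. It is a real limit on how a longer SADE outcome can be read, but it applies equally to the in-hospital SADE outcome already listed.

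It could also be said that an extra safety table belongs in the analysis plan. That would be so if the article left the window open, but it fixes it.

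**Conclusion.** The point holds as a specific and inexpensive improvement to a stated outcome window. The SADE outcome stops at the end of the index stay, while SAEs run to 365 days and device-related events are to be reported and listed with no stated cut at discharge. After discharge, no listed outcome compares the arms on events classified as device-related. The events themselves remain in all-cause SAEs, deaths and the limb outcomes.

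The size cannot be fixed from the article. Under the assumed rates, the half-width for a 2-point excess is roughly 2.4 to 4 times wider within all-cause SAEs than as SADE (5.37/2.27 = 2.4; 5.80/1.41 = 4.1). Power as SADE ranges from 0.41 to 0.80 for that excess, against about 0.10 to 0.11 within SAEs. All of this rests on 570 evaluable patients per arm, assumed rates and unbiased causality labels, and should be taken as illustration only. The primary non-inferiority conclusion is unaffected. The full protocol, which holds the SADE definitions, is not shown.

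**What to change.** In the Safety outcomes list, give SADE the windows already used for SAEs: the index stay, 30 to 180 days, and 365 days. Report it by arm with a risk difference and 95% confidence interval, using the causality classification already made for section {22}. If the cut at discharge is deliberate, state the reason instead.

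Two safeguards belong with the change. Check that the SADE definition in the full protocol classifies events related to the comparator balloon in the same way as those related to the coated balloon, so that the arms can be compared. State that SADE is to be read beside all-cause SAEs and deaths, because causality is judged open-label and may be labelled differently by arm.

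The cost is one line in the outcome list, one table and an amendment. No visit or data item is added, since SAEs are already collected to 365 days and their relation to the device is already considered for reporting.
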